### Development and piloting the Fit Joints intervention

Due to the complexity of the frailty syndrome, we are developing the proposed multi-modal frailty intervention using the revised Medical Research Council framework for design and evaluation of complex interventions [26, 27]. The FIT trial in Australia demonstrated successful frailty reduction after implementing a 1-year frailty intervention tailored to each participant based on comprehensive geriatric assessment. The target cohort was frail patients (three or more Fried criteria) seen in an aged care service [18].

### Multi-modal Fit Joints intervention components

The intervention and outcome assessment visits are summarized in Fig. 3.

**Fig. 3 Fig3:**
[figure not shown]
Study intervention and outcome assessments. The square means a visit and the circle means a phone call

Participants in the intervention group will receive, for up to 10 months, a multimodal program intended to target frailty reduction (as described in Table 1) between randomization and their surgery. The study intervention kinesiologist will manage the coordination of the exercise components of the intervention, and deliver vitamin D and protein supplementation. The study geriatrician will provide the medication review component, and 2 of the study investigators who are expert in nutrition will review the vitamin D and protein supplementation.

**Table 1 Tab1:** Components of the multimodal intervention

Component	Dose/material provided	Description
Exercise and coaching	Based on Canada’s Physical Activity Guidelines^1^ Minimum: 3× week for 45–60 min at home and/or YMCA [28, 44]	• Kinesiologist assessment: goal setting, cognitive behavior change strategies^2^ • HOME: tailored exercise program based on individual ability and exercise preference (i.e., chair versus standing exercises). Functional movements to mimic ADL’s (i.e., getting up from a chair). Exercise bands will be provided. • All participants will progress based on their current physical activity levels while focusing on personal fitness and health goals set at the beginning of the program. • YMCA: InMotion program • GOAL: endurance, resistance, and balance training 3× week for 45–60 min at home and/or YMCA • Monthly kinesiologist visit/bi-weekly phone calls [28]. • Participants will track their exercise in a study-tracking logbook.
Protein	1–2 Ensure Enlive™ protein daily	• Each serving (vanilla or chocolate flavor) contains 350 kcal, 20 g protein, 1.5 g β-Hydroxy β-Methylbutyrate (HMB) • Advised to take the protein supplement with a meal or within 3 h of exercise on activity days [32, 33]. • Pre-albumin serum level tested at the screening and 6-week postoperative visits (carried out by the clinic nurse during these visits).
Vitamin D	1 × 1000 IU/day, unless prescribed otherwise by family physician.	• Vitamin D3 (1000 IU tablets) • Serum 25 (OH). Vitamin D serum level tested at the screening and 6-week postoperative visits.
Medication review		• A pharmacist trained geriatrician ([name]) will review the medications of participants in the intervention arm using subsets of Beers [45] and STOPP/START criteria [46] to check for any inappropriate medications. • Any recommendations will be mailed/faxed to the participants’ family physicians for their consideration by the central site coordinator.

^1^Based on Canadian Physical Activity Guidelines for those aged 65 years or older which recommend cardiorespiratory, strength, balance, and flexibility exercise components [25]

^2^Topics to support patients in achieving their health goals could include (1) goal setting, (2) self-monitoring, (3) time management, (4) overcoming barriers, (5) environmental scan, (6) social support, and (7) stimulus control

### Kinesiologist visit schedule and delivery of coaching/supplements

After randomization, the study intervention kinesiologist will phone the participant to book a home visit where goal setting will be done. During months 2–10, the study intervention kinesiologist will have bi-weekly contact (one monthly visit and one phone-call in the interim) [28] to check on progress. At the visits, the kinesiologist will adjust programs as needed, provide ongoing coaching/education, and deliver vitamin D/protein supplements. We will use exercise-reporting guidelines (CERT) to guide reporting the exercise component of the intervention [29]. Participants will be encouraged to use the Borg Rating of Perceived Exertion 10-point Scale to monitor their perceived effort levels and exhaustion for each exercise component (1 means rest/no effort and10 means maximal effort) [30]. Participants will be asked to work in a 5–7/10 workload (i.e., 50–60% of their maximal heart rate). The Borg Scale will help participants to work based on how they are feeling, which is safer for the geriatric population. In the first intervention visit, the study kinesiologist will ask the participants if they would prefer to do center-based or home-based exercise, or both.

### Center-based exercise

If a participant decides to do center-based exercise, they will be provided with a free membership of the YMCA community center to participate in the “InMotion program”. This community-based program is designed for people with chronic bone and joint health problems such as osteoporosis and arthritis. It is also appropriate for those wanting to improve their health before and after having hip or knee replacement surgery. Fitness trainers lead the InMotion program, and if needed, an experienced physiotherapist is available for consultation. The program includes hydrotherapy, aerobic exercise, and 12 education sessions. Participants will be encouraged to attend the InMotion program components at least three times per week. Additional file 2 shows further description to the Fit Joints exercise.

### Cognitive behavioral change strategies (CBCS)

The participant’s readiness to exercise and their exercise barriers/facilitators will be determined using a self-reported questionnaire guided by the trans-theoretical model of behavior change (TTMBC) [31, 32]. Based on the participant’s readiness to exercise, CBCS may be an effective way to promote exercise in older adults [33]. In the current study, the administration of the modules will be dependent on the challenges that the participants express using the exercise barrier/facilitators questionnaire (i.e., lack of time, motivation, social support). These strategies are based on the TTMBC [31, 32]. The 7 CBCS topics that will be incorporated over the intervention period will include (1) goal setting: to assist with the development of their tailored exercise program, (2) self-monitoring: to track their exercise progress/goals/behavior, (3) time management strategies: to find more time to exercise, (4) overcoming barriers: to overcome adversity in exercise routines, (5) environmental scan: to help participants identify local/available resources and support, (6) social support: to find participants’ support system to achieve physical activity, and (7) stimulus control: to create participants’ planned reminders for increasing physical activity.

### Control group

Patients in the control group will receive usual care, which may include recommendations from their orthopedic surgeon to attend exercise programs, fitness and educational classes, physiotherapy referral, pool therapy, or weight loss program before surgery. However, these patients will not receive any support from the study intervention kinesiologist. Participants in the control and intervention groups will be instructed to complete a dietary intake log (including days of the week and weekend days) that indicates the type of food and amount ingested over a 4-day period in order to calculate energy and micronutrient consumption.

### Study outcomes

#### Primary outcome: feasibility

Feasibility will be assessed by (1) recruitment rate, (2) retention rate, and (3) data collection completion [22]. Figure 2 summaries the primary and secondary outcomes and measurement time. The Fit Joints intervention fidelity (the degree to which the Fit Joints intervention is delivered) will be assessed by measuring the length of the intervention and number of intervention components delivered by the study kinesiologist. We will measure participants’ adherence to each component of the intervention (center-based or home exercise, protein and vitamin D supplement, and medication review). Adherence will be measured by a monthly self-reported form developed specifically for the Fit Joints trial.

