### Data analysis

Data from the trial will be analyzed and reported in accordance with the CONSORT criteria [33, 39]. The baseline characteristics will be reported as mean (standard deviation) or median (inter-quartile range) values for continuous variables and as counts (percent) for categorical variables. Data will be summarized in tabular or graphical form. The main between-group comparison will take place at 6 weeks post-operative. The primary feasibility outcomes will be analyzed using descriptive statistics expressed as percent and corresponding 95% confidence intervals (CI). For clinical outcome, analyses will be performed using the intention-to-treat principle. We will use linear regression for continuous variables and logistical regression for categorical variables to explore the difference between groups pre- and post-operative. Exploratory subgroup analyses will be conducted to explore the differential effect of home-based versus center-based exercise and the effect on people undergoing hip versus knee replacement. Sensitivity analysis will be conducted using the per-protocol concept (including adherent participants, who completed 70% of the intervention components (i.e., completed 70% of exercise sessions, took 70% of the vitamin D, protein supplements, and the medication review was done)) [40]. All *p* values will be reported to three decimal places with those less than 0.001 reported as *p* < 0.001. The criterion for statistical significance will be set a priori at alpha = 0.05. Analyses will be performed using STATA V13 [41].

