Medical Research Council criteria define a “complex intervention” as interventions that are built up from a number of components, which may act both independently and inter-dependently [44]. These components include behaviors, behavior parameters, and methods of organizing those behaviors, and they may have an effect at the individual patient level, organizational, or service level or population level (or all of these in some cases). As any complex intervention, the Fit Joints intervention has several articulating components (including center and/or home-based tailored exercise program, cognitive behavioral coaching, protein and vitamin D supplements, and medication review). It is a challenge to (1) standardize all these intervention components and (2) determine the contribution of each intervention component and any interaction between these components [25]. Phase 0 (choosing an intervention theoretical model) and phase 1(identify the intervention components and the supporting evidence) of the Medical Research Council framework have been completed. The proposed study represents phase 2 of the Medical Research Council framework (which is examining the feasibility of the intervention). After completing this pilot study, we will complete phase 3 (definitive study) and phase 4 (dissemination and implementation).

The proposed study has some limitations. Participant recruitment will take place within one hospital site, which may limit its generalizability to other hospital care settings. Fit Joints investigators have considered the challenge of applicability to other settings during the study protocol development. Participants will be offered to do center-based or home exercise; however, some participants may not have access to the center-based exercise due to various reasons such as lack of time or transportation. Also, the pre-operative assessments will occur in different time points for different participants due to the variable intervention duration and that might lead to heterogeneity of the intervention effect across participants.

Strengths of our proposed study include (1) valid and reliable patient reported measures were used; and (2) Fit Joints study engaged all key stakeholders in the process of implementation, including patients, interdisciplinary healthcare teams, community organizations, and researchers. Having each perspective will enhance the participants experience throughout the study course.

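### Adherence, and the 70% per-protocol set built on it, rest on a participant-completed form alone and cannot be checked, although supplements could be counted at visits already planned

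*Protocol article*

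**What the plan says.** Under Primary outcome: feasibility, adherence is to be measured for each component: "center-based or home exercise, protein and vitamin D supplement, and medication review". The instrument follows: "Adherence will be measured by a monthly self-reported form developed specifically for the Fit Joints trial". Fidelity is a separate quantity, assessed by "measuring the length of the intervention and number of intervention components delivered by the study kinesiologist". It describes what was delivered, not what was taken or done.

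The Data analysis section plans one sensitivity analysis by name, per protocol, "including adherent participants, who completed 70% of the intervention components". The rule is spelled out as: "completed 70% of exercise sessions, took 70% of the vitamin D, protein supplements, and the medication review was done". The main clinical analysis is by intention to treat.

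Two features of delivery matter here. At the monthly visits the kinesiologist will "provide ongoing coaching/education, and deliver vitamin D/protein supplements". Participants who choose the center are told that "they will be provided with a free membership of the YMCA community center". Neither section mentions counting unused product or using attendance records.

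**The concern.** Participants know their allocation. The person who sets goals with them and coaches them also visits monthly and brings the supplements. The form asks them to account for a month of daily supplements and of exercise at least three times a week. Over-reporting in that setting is a plausible risk.

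Two results depend on the form. One is the descriptive adherence figure, which a later multi-center trial would use to judge whether the bundle can be delivered; the Background criticises earlier trials for not reporting adherence. The other is the per-protocol set. Because that set is cut at a threshold, an error in the form moves people across the line and mixes non-adherent participants into a group labelled adherent.

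**Working it through.** **1. The plan's own figure.** Inputs from the Sample size section: proportion 0.80, half-width 0.10, two-sided 95%. n = 1.96² × 0.80 × 0.20 / 0.10² = 61.46, rounded up to 62, as stated. At n = 62 the half-width is 9.96 points. Adherence does not enter this calculation. With 1:1 allocation the intervention arm has about 62 / 2 = 31 participants.

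**2. What records exist, by component.**

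| Component | Participant-reported | Other record described | Linked to adherence or the 70% rule? |
|---|---|---|---|
| Vitamin D, protein | Monthly form; supplement items on the healthcare-use form; 4-day food log | Serum 25(OH)D and pre-albumin at screening and 6 weeks after surgery | Form only |
| Center exercise | Monthly form; logbook | None; membership provided | Form only |
| Home exercise | Monthly form; logbook; home-session count on the healthcare-use form | None | Form only |
| Medication review | Monthly form | Done by the study geriatrician | Form only |

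The intervention runs from randomization to surgery, so the second blood sample falls six weeks after it has ended. It cannot stand in for a count of units taken.

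**3. What misreporting would do to the adherent set.** Let t be the share of the arm that truly meets the whole rule, s the share of those whom the form classes as adherent, and f the share of the others whom it also classes as adherent. Then

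- reported share r = t·s + (1 − t)·f
- wrongly included fraction of the adherent set m = (1 − t)·f / r

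The article gives none of these values; all are assumptions. With t = 0.50 and s = 1:

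| f | r | Number of 31 | m |
|---|---|---|---|
| 0 | 50% | 15.5 | 0% |
| 0.10 | 55% | 17.1 | 9% |
| 0.20 | 60% | 18.6 | 17% |
| 0.30 | 65% | 20.2 | 23% |
| 0.50 | 75% | 23.2 | 33% |

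If s = 0.90, then f = 0.10 gives 0.45 + 0.05 = 50%, no net error, and f = 0 gives 45%, an understatement. At f = 0.20 and s = 1, the result for t = 0.40 is r = 52% and m = 23%; for t = 0.70 it is r = 76% and m = 8%.

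**4. The cut-off itself.** If reported doses exceed true doses by a factor of 1.1, 1.2 or 1.3 (assumed), a reported 70% corresponds to 70/1.1 = 64%, 70/1.2 = 58% or 70/1.3 = 54%.

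**5. A count needs a denominator.** Table 1 gives protein as one to two servings daily. One serving a day is 1/1 = 100% of an assignment of one and 1/2 = 50% of an assignment of two, on opposite sides of 70%. Any count must therefore be set against the amount assigned to that participant.

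**The case against.** **The article is condensed.** Product accountability could sit in a full protocol that is not shown. If it does, citing it settles the supplement part. But the article does not leave the method open. It states the adherence instrument, and the concern is with that stated choice.

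**Other data exist.** The logbook, the food log, the healthcare-use form and the blood tests allow some cross-checking. This stands in part. The first three are participant-reported as described, the blood tests come too late, and none is tied to the 70% rule.

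**The error has no known sign.** A reader might infer that adherence will be overstated, or by some stated factor. The article does not support that: step 3 runs from −5 to +25 points on assumed inputs alone. Nor would a model of one overall completion percentage give the size, because the rule is joint. If 35% met each of three components independently, only 0.35³ × 31 ≈ 1.3 participants would meet all three, against about 11 if the components moved together.

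**The Discussion.** A reader might also see a contradiction with the stated strength that "valid and reliable patient reported measures were used". That sentence does not mention the adherence form and reads naturally as being about outcome instruments. It is not a contradiction.

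**The alternative is partial.** A membership does not prove that attendance is logged or obtainable, and home exercise has no objective source. Both limits stand.

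**The consequence is small.** Adherence is not one of the three named feasibility criteria, and self-report is a common pragmatic choice. This stands and limits the weight of the point.

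**Conclusion.** The point holds in a limited form. The 70% set has no stated source other than the self-reported form, so adherence and the adherent set may be overstated and the plan describes no way to find out. The documents fix neither direction nor size, and the figures in steps 3 and 4 only show how sensitive the set is. What is affected is the descriptive adherence result and the per-protocol sensitivity analysis. Recruitment, retention, data completion, N = 62 and the intention-to-treat analysis are not. This is a modest improvement, worth making because the visits needed for it are already in the schedule.

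**What to change.** - At each monthly kinesiologist visit, record units of vitamin D and of protein drink delivered and left, with the amount assigned to that participant as denominator.
- Request center attendance, with the participant's consent, where records exist.
- Take completion of the medication review from study staff records.
- State that these sources define the 70% rule, and that self-report is used for home exercise.
- Keep the form for all components and report the gap between self-report and counts as a pilot result.

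The cost is a few minutes per existing visit, a few form fields and an attendance request to the center. Counts miss product that is shared or thrown away, and for home exercisers part of the rule still rests on self-report. The article describes recruitment as ongoing, so the change can apply to visits still to come. Where no count was made, label the adherence result as self-reported.

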#### Secondary outcomes

Frailty will be assessed using (1) Fried frailty phenotype which is composed of five items, three self-reported (unintentional weight loss, exhaustion and physical activity), and two performance-based items (strength (assessment based on the handgrip strength measurement) and gait speed). It is a widely used and validated frailty measure [11, 34]. Each item is scored 0 or 1 with a final score out of 5; higher scores indicate greater frailty; and (2) short performance physical battery (SPPB) (made up of three assessments [35]: (a) the 4-m walk test (walking speed); (b) chair rise: balance and coordination (the ability to rise from a chair without arms); and (c) the standing balance test). The participant is evaluated on each assessment using a score between 0 and 4. A final summary performance score out of 12 is calculated, with higher scores indicating superior lower extremity function [35]. The SPPB has also been validated and has demonstrated good internal consistency and responsiveness [36, 37]. Healthcare service use (including patients’ medications/supplements (dose, frequency, and duration), discharge destination, length of hospital stay, rehospitalization rate, number of visits to general practitioner, emergency room, specialists, and physiotherapist, and number of home exercise sessions) will be collected using a form specifically developed for this study. Other outcomes listed in Fig. 2 will be collected. The study outcomes will be collected at the baseline, 1 week pre-operative, and 6 weeks and 6 months post-operative.

### Adverse events

Adverse events or harm from any source will be reported to the research team and recorded on a structured form. Any serious adverse events will be reported to the Research Ethics Board within 24 h. Participants will be instructed to contact the study coordinator if they experience any unfavorable/unintended signs or symptoms. An independent Data Safety and Monitoring Committee will review safety data from the trial and advise the investigators and the Steering Committee on the future management of the trial.

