### Data collection and management

Figure 2 provides an overview of the data collection timeline. The baseline and 1-week preoperative assessments will be conducted in the participant’s home, and the 6-week and 6-month assessments will be conducted in the orthopedic clinic. All four assessments will be conducted by blinded assessors. The study assessors received an individualized 3-day training on how to collect the study outcome measures from frail older adults. Study data will be managed using REDCap electronic data capture tools [38]. The study database will be password protected and kept on a secure network system.

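### Before surgery only the intervention arm has regular staff contact, so adverse events recorded from any source are likely to be more complete in that arm

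*Protocol article*

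**What the plan says.** The Adverse events section makes two statements about collection. The first is general: "Adverse events or harm from any source will be reported to the research team and recorded on a structured form". The second is the only route described at participant level: "Participants will be instructed to contact the study coordinator if they experience any unfavorable/unintended signs or symptoms". An independent committee then reviews the safety data and advises on the future of the trial. The Theory and development framework section lists treatment safety among the matters the pilot is to assess.

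Contact with staff before surgery differs by arm. The program runs between randomization and surgery: "Participants in the intervention group will receive, for up to 10 months, a multimodal program intended to target frailty reduction". It begins with a home visit, and for months 2 to 10 "the study intervention kinesiologist will have bi-weekly contact (one monthly visit and one phone-call in the interim". For controls, the Control group section says "these patients will not receive any support from the study intervention kinesiologist", and no equivalent contact is described.

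Some collection is shared. Assessments take place at baseline, 1 week before surgery, and 6 weeks and 6 months after it. On these, Data collection and management states: "All four assessments will be conducted by blinded assessors". Healthcare service use, including emergency room visits and rehospitalization, "will be collected using a form specifically developed for this study". A monthly form also exists, but it is described for another purpose: "Adherence will be measured by a monthly self-reported form developed specifically for the Fit Joints trial".

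**The concern.** Whether an event reaches the structured form depends on whether it occurred and on whether anyone in the study heard of it. Controls with a minor fall, a painful joint or an upset stomach during the wait must decide to call the coordinator. Intervention participants can do the same, but they also talk regularly with a staff member who checks progress and adjusts the exercise program. What is mentioned there falls under the any-source rule. After baseline, participants know their group, and the coordinator who takes the calls is unblinded, so nothing offsets the difference in opportunity.

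At stake is the comparison of harms between arms, which bears on a stated aim of the pilot, on the committee's advice and on the design of the later multi-center trial. The likely direction is against the intervention. If the source of each report is not recorded, the effect cannot be separated out afterwards.

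**Working it through.** **Is there a figure to reproduce?** The plan gives no adverse-event rate and no capture rate, so there is no safety figure. The sample size is used below only for the number per arm, and it reproduces: 1.96² × 0.8 × 0.2 / 0.10² = 61.46, rounded up to 62. With 1:1 allocation that is 31 per arm.

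**Pre-operative contacts.** Inputs are the first home visit and one visit plus one call a month from month 2 (Kinesiologist visit schedule), and a wait of 3 to 10 months (Eligibility criteria). I assume one contact in month 1. For a wait of m months, contacts = 1 + 2 × (m − 1).

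| Wait (months) | Intervention | Control (described) |
|---|---|---|
| 3 | 1 + 2 × 2 = 5 | 0 |
| 6 | 1 + 2 × 5 = 11 | 0 |
| 10 | 1 + 2 × 9 = 19 | 0 |

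These exclude the assessments common to both arms. Table 1 can be read as allowing more calls; the section text gives the smaller count.

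**Which events are affected?** Setting the sections side by side:

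- Events leading to an emergency room visit, a rehospitalization or a visit to a general practitioner, specialist or physiotherapist have a route through the healthcare-use form, with no difference by arm stated.
- After surgery, scheduled contact is the same in both arms.
- What remains is pre-operative events that lead to no counted care. For these the text describes a participant's call in both arms and offers kinesiologist contacts in one arm only.

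**How unequal capture would act.** Recorded risk = true risk × capture probability. With equal true risk, the ratio of recorded risks equals the ratio of capture probabilities, whatever the true risk. The figures below assume a true risk of 30% and 31 per arm. The risk and the capture values are assumptions, not estimates for this trial.

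| Capture, intervention v control | Expected participants with a recorded event | Ratio |
|---|---|---|
| 90% v 90% | 8.4 v 8.4 | 1.0 |
| 90% v 70% | 8.4 v 6.5 | 0.90 / 0.70 = 1.29 |
| 70% v 50% | 6.5 v 4.65 | 0.70 / 0.50 = 1.40 |
| 90% v 50% | 8.4 v 4.65 | 0.90 / 0.50 = 1.80 |

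The first row uses 31 × 0.30 × 0.90 = 8.4 in each arm; the others follow in the same way. The table shows direction and mechanism. It does not say which row applies here.

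**The case against.** The strongest reply is that this is a condensed article. Telling participants to call does not exclude asking them at visits. Fig. 2, to which the outcome and data-collection sections refer, is not shown and may list adverse-event questions. Nothing says that the kinesiologist asks about or records harms. The healthcare-use form and four blinded assessments serve both arms. The Data analysis section names no between-arm test of adverse events, and 31 per arm is small: for assumed recorded risks of 27% v 15% the standard error of the difference is √[(0.27 × 0.73 + 0.15 × 0.85) / 31] = 0.10. Unequal contact is also inherent in comparing a coached program with usual care.

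Much of this stands as a limit. A reader might infer that the trial relies wholly on participants calling in, that recorded harms will certainly differ by arm, or that the excess can be put at a given number of points. The documents support none of these. The any-source rule is wider than calls, no capture rates are stated, and any figure for the excess restates whatever rates are assumed.

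It does not remove the point. Even if questions are asked at the common visits, the any-source rule adds to them whatever emerges at kinesiologist contacts, and those exist in one arm. No formal collecting role is needed for complaints to be mentioned while a program is being adjusted. Small numbers make formal inference weak, but the committee will still see the counts, and this imbalance does not shrink with more participants. Unequal contact may be unavoidable; letting the safety comparison depend on it is not.

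**Conclusion.** The concern holds as a likelihood, for a limited class of events. Recorded pre-operative adverse events, mainly milder ones that lead to no care on the healthcare-use form, are likely to be more complete in the intervention arm. A between-arm summary pooling all sources may therefore overstate harm from the intervention.

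What the document fixes is the difference in opportunity: about 5 to 19 extra pre-operative contacts against none described. The resulting excess cannot be derived. The conclusion assumes that some complaints are mentioned at kinesiologist contacts that would not otherwise be phoned in, and that all recorded events enter one comparison. If capture is equal in practice, the ratio is 1.0 and there is no bias. The sample size of 62 is unaffected. The change is worth making because safety is a stated aim of the pilot and the source of a report is hard to reconstruct later.

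**What to change.** 1. At the three post-baseline assessments common to both arms (1 week before surgery, 6 weeks and 6 months after), collect adverse events with the same scripted questions and look-back period in both arms. Baseline is left out because it precedes the intervention and yields no treatment harms.
2. Ask after the performance tests or, better where the same assessor may return for the 6-week comparison, use a self-completed form that the assessor does not read. Complaints about exercise or supplements could otherwise reveal the group.
3. Base the between-arm safety table and the monitoring committee's comparison on these events and on healthcare-use events.
4. Add a source field to the structured form. List events learned only through kinesiologist contacts or spontaneous calls separately, by arm.
5. Keep the reporting of serious events from any source as it stands.

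If Fig. 2 or the full protocol already provides identical questioning, items 3 and 4 and one clarifying sentence in the Adverse events section suffice.

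The cost is a few minutes per existing visit and one field on an existing form. Recall at the pre-operative visit covers up to about 10 months, so some minor events will be lost in both arms. For a given wait the recall period is the same in each arm, and randomization is stratified by approximate waiting time. Because recruitment has begun, the change would start part-way, and source should be filled in for events already recorded where it is known.
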